### ***Severity of bleeding complication***

The ISTH/SSC proposed a bleeding assessment tool that facilitates the diagnosis of less symptomatic mild bleeding disorder and the grading of severity in patients with known inherited bleeding disorders. For each specific bleeding symptom, a score of 1 or more is classified as significant.

### ***Readmissions within 3 months after discharge***

Three months after hospitalization the patient receives a small questionnaire about the use of healthcare. The questionnaire asks for visits to the general practitioner or the hospital because of a bleeding or thrombotic event within 3 months after hospitalization.

The hospital information system is used to register readmissions and the reason for readmission of the patients in the same hospital. The patient's general practitioner is asked for readmissions in other hospitals. Only the patient's first hospital admission is included in the study period (readmissions are the secondary outcome measures).

It will take about 5 minutes to fill out the questionnaire.

### ***Quality of life***

At discharge the patient (or the parents/guardian of the patient) will be asked to fill out a consent form. After the patient (or the parents/guardian of the patient) has signed the consent form, he or she receives a EuroQol EQ5D questionnaire 3 months after hospitalization. The questionnaire will ask for the quality of life. The age range of patients of the quality of life version is as follows:

- Age 0-3: no EQ-5D-Y is available.
- Age 4-7: EQ-5D-Y proxy version 1: the proxy rates how he/she rates the health of the child.
- Age 8-11: EQ-5D-Y or EQ-5D-Y proxy version 1: Generally EQ-5D-Y is recommended. However, EQ-5D-Y proxy version 1 is usable for children of 8+ who are not able to fill in the EQ-5D-Y themselves.
- Age 12-15: EQ-5D-Y or EQ5D: Generally EQ-5D-Y is recommended.
- Age 16 and older: EQ5D

It will take about 5-10 minutes to fill out the questionnaire.

### ***Adherence by the patient to the therapy***

At discharge the patient (or the parents/guardian of the patient) will be asked to fill out a consent form. After the patients (or the parents/guardian of the patient) has signed the consent form they are asked 3 months after hospitalization to fill out a questionnaire about their adherence to drug treatment (MARS; Medication Adherence Rating Scale). Adherence to medication is assessed using a five-item self-report scale called the Medication Adherence Report Scale 5 (MARS5). The MARS5 contains five items to which respondents rate their

agreement on a five-point scale. Scores for each of the five items are summed to give a total adherence score between 5 and 25, where higher scores indicate higher levels of adherence. The age range of patients is as follows:

- Age 0-8: the questionnaire is filled out by the parents/guardian of the patients.
- Age  $\geq 9$ : the questionnaire is filled out by the patient himself. (A child's ability to respond to the questionnaire was determined by his/her physician).

It will take about 5 minutes to fill out the questionnaire.

#### ***Patient satisfaction with the quality of care of the antithrombotic therapy***

At discharge the patient (or the parents/guardian of the patient) will be asked to fill out a consent form. After the patient (or the parents/guardian of the patient) has signed the consent form, he or she receives a VAS satisfaction scale 3 months after hospitalization. The questionnaire will ask for the satisfaction with the quality of care.

It will take less than 1 minute to fill out the questionnaire.

#### ***Bleeding (major bleeding and mild to moderate clinical relevant non-major bleeding) or thrombotic event within 3 months after hospitalization***

Three months after hospitalization the patient receives a small questionnaire about the use of healthcare. One of the questions is whether the patient visited the general practitioner or the hospital because of a bleeding or thrombotic event within 3 months after hospitalization.

#### ***Adherence to the hospital protocol***

Information from the medical record of the hospital information system will be used to verify the adherence by the doctors to the antithrombotic hospital protocol.

#### ***Cost-effectiveness analysis***

The aim of the economic evaluation is to determine whether the implementation of the S-team contributes to a reduction of the healthcare costs. All costs of healthcare are assessed as it is hard to distinguish which costs are related to medication use. Healthcare costs include the costs of hospitalizations for bleeding/thrombotic events, labor costs and medication costs (including the use of antidotes).

#### ***Medication use three months before and three months after hospitalization***

Medication records of the community pharmacy can be consulted through a link in the hospital information system for patients that are within the catchment area of the hospital. If a community pharmacist is not connected to the hospital information system, the hospital pharmacy will obtain a faxed medication list from the community pharmacist.

#### ***All-cause mortality***

We define all-cause mortality as death from any cause during and 3 months after hospitalization.

#### ***Percent time in therapeutic range of vitamin K antagonists***

INR data are collected during and 3 months after hospitalization. Therapeutic INR range (TTR) is a way of summarizing INR control over time.

### **8.3.2 Implementation phase**

The intervention consists of the implementation of the S-team. The S-team consisting of a specialized thrombosis nurse as case manager, hematologist, medical leader Thrombosis Service, hospital pharmacist/clinical pharmacologist, cardiologist and a pediatric hematologist. An anesthesiologist, neurologist, pulmonologist, dermatologist, clinical chemist, emergency physician and (orthopedic) surgeon may be added to the team when necessary.

### **8.3.3 Post-intervention phase**

During a 9-month period the S-team is active. From the clinical rule patients with antithrombotics will be identified and presented to the S-team. The main tasks of the S-team will be:

- Drafting of local guidelines
- Monitoring of the medication by the hospital pharmacist/clinical pharmacologist focused on patients that are treated with antithrombotics
- Patient instructions
- Proper handover to either the Thrombosis Service or the general practitioner, and to the community pharmacist, at the moment of hospital discharge
- Educating physicians, nurses and hospital pharmacists
- Offering consultation for professionals in- and outside the hospital

During the post-intervention phase the same data are collected as during the pre-intervention phase.

## **8.4 Withdrawal of individual subjects**

N.a.

### **8.4.1 Specific criteria for withdrawal**

N.a.

## **8.5 Replacement of individual subjects after withdrawal**

N.a.

## **8.6 Follow-up of subjects withdrawn from treatment**

N.a.

## **8.7 Premature termination of the study**

N.a.

## 9. SAFETY REPORTING

### 9.1 Section 10 WMO event

In accordance to section 10, subsection 1, of the WMO, the investigator will inform the subjects and the reviewing accredited METC if anything occurs, on the basis of which it appears that the disadvantages of participation may be significantly greater than was foreseen in the research proposal. The study will be suspended pending further review by the accredited METC, except insofar as suspension would jeopardize the subjects' health. The investigator will take care that all subjects are kept informed.

### 9.2 AEs, SAEs and SUSARs

#### 9.2.1 Adverse events (AEs)

Adverse events are defined as any undesirable experience occurring to a subject during the study, whether or not considered related to the implementation of the S-team. All adverse events reported spontaneously by the subject or observed by the investigator or his staff will be recorded.

#### 9.2.2 Serious adverse events (SAEs)

A serious adverse event is any untoward medical occurrence or effect that at any dose:

- results in death;
- is life threatening (at the time of the event);
- requires hospitalization or prolongation of existing inpatients' hospitalization;
- results in persistent or significant disability or incapacity;
- is a congenital anomaly or birth defect;
- any other important medical event that may not result in death, be life threatening, or require hospitalization, may be considered a serious adverse experience when, based upon appropriate medical judgment, the event may jeopardize the subject or may require an intervention to prevent one of the outcomes listed above.

The sponsor will report the SAEs through the web portal *ToetsingOnline* to the accredited METC that approved the protocol, within 15 days after the sponsor has first knowledge of the serious adverse events.

SAEs that result in death or are life threatening should be reported expedited. The expedited reporting will occur not later than 7 days after the responsible investigator has first knowledge of the adverse event. This is for a preliminary report with another 8 days for completion of the report.

This section is not applicable for this quality project

#### 9.2.3 Suspected unexpected serious adverse reactions (SUSARs)

N.a.

### 9.3 Annual safety report

N.a.

**9.4 Follow-up of adverse events**

All AEs will be followed until they have abated, or until a stable situation has been reached. Depending on the event, follow up may require additional tests or medical procedures as indicated, and/or referral to the general physician or a medical specialist. SAEs need to be reported till end of study within the Netherlands, as defined in the protocol

**9.5 [Data Safety Monitoring Board (DSMB) / Safety Committee]**

N.a.

## **10. STATISTICAL ANALYSIS**

### **10.1 Primary study parameter(s)**

The database will be made in Open Clinica (open source clinical trial software for Electronic Data Capture (EDC) Clinical Data Management (CDM)) and the results will be analyzed with a statistical analysis software program (SPSS).

For the primary outcome interrupted time series analysis will be used for data-analysis. The primary outcome will be compared using univariate and multivariate logistic regression analysis.

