### 4.4 Sample size calculation

In studies major bleeding complications tend to occur in about 2-3% of all patients per year on antithrombotics, but in every day practice it seems this rate is at least 10%. Conservatively, we will presume a rate of 5%. Thrombotic events are estimated to occur in 3% of treated patients per year in studies. As trials form the ideal situation, we assume this is the rate we could achieve with the S-team and that the rate is 4% in the pre-intervention period. This results in a composite rate of 9% and we expect to decrease this to 2.5% bleeding events and 3% thrombotic events (composite 5.5%). With an alpha of 0.05 and power of 0.80 the required sample size will be 917 patients in the pre-intervention phase and 917 patients in the post-intervention phase. In order to account for drop-outs 1900 patients will be included.

In a (not yet published) study aiming at the development of a prediction rule for VKA-related International Normalized Ratio (INR) elevation from our Erasmus MC group 3800 patients using VKAs were included over 4 years. Thus within 9 months over 700 patients using VKAs will be admitted to the Erasmus MC alone. As we include another hospital and other antithrombotics as well, we expect that 9 months will be sufficient to recruit the required number of patients.

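### Section 4.4's power of 0.80 holds only for a before-after comparison without a time trend, but section 10.1 names interrupted time series for the primary outcome and does not say which analysis decides.

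*Protocol*

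**What the plan says.** Protocol section 10.1 gives the primary outcome two consecutive sentences. The first is "For the primary outcome interrupted time series analysis will be used for data-analysis". The second is "The primary outcome will be compared using univariate and multivariate logistic regression analysis". Neither analysis is labelled main or supportive, and nothing links them.

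Section 4.4 assumes that the composite falls from 9% to 5.5% and then states: "With an alpha of 0.05 and power of 0.80 the required sample size will be 917 patients in the pre-intervention phase", with the same number in the second phase. It mentions no time trend, number of time points or autocorrelation. Recruitment is raised to 1900 in total for drop-outs.

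Section 8.3 describes a pre-intervention phase, an implementation phase and a post-intervention phase. Usual care is observed for 9 months (section 8.3.1). For the last phase, section 8.3.3 says "During a 9-month period the S-team is active". The text gives no length for the implementation phase; Figure 1, which might show it, was not available to this review.

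**The concern.** The two named methods answer different questions. ITS with a trend term asks whether the event rate shifted at the intervention beyond where the existing trend was heading. A logistic comparison of phases without a time term asks whether the later patients had fewer events than the earlier ones, for whatever reason. Section 3 describes an uncontrolled before-after design and section 8.2 marks randomisation as not applicable, so a secular trend is the main rival explanation. This is the setting in which the two answers may differ.

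They also differ sharply in precision. Within two adjacent 9-month blocks, calendar time and phase are strongly correlated, and a model that estimates both pays heavily in variance. A sample size set for the comparison without a trend cannot lend its power to the one with a trend. If ITS decides and the planned effect is real, the study would probably miss it, and readers holding a stated power of 0.80 could take the null result as evidence of no benefit.

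**Working it through.** **Inputs.** From section 4.4: p1 = 0.09, p2 = 0.055, alpha 0.05, power 0.80, n = 917 per phase. From sections 8.3.1 and 8.3.3: 9 months per phase. Assumed, because the protocol does not give them: two-sided alpha, monthly points (917/9 ≈ 102 patients, about 9.2 events a month before and 5.6 after), an immediate step, no true underlying trend, no autocorrelation.

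**Step 1: reproduce 917.** With mean proportion 0.0725:

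n0 = [1.96·√(2·0.0725·0.9275) + 0.8416·√(0.09·0.91 + 0.055·0.945)]² / 0.035² = (0.7188 + 0.3079)² / 0.001225 = 860.5

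Continuity correction: n = (n0/4)·[1 + √(1 + 4/(n0·0.035))]² = 916.8, so **917**.

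Other versions do not match: 861 two-sided uncorrected, 858 unpooled, 850 arcsine, and 678 or 734 one-sided. The protocol's number is a two-proportion calculation and is correct as such.

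**Step 2: power without a trend term.** The log odds ratio is ln(0.09/0.91) − ln(0.055/0.945) = 0.530 in absolute size. Its variance is 1/(917·0.0819) + 1/(917·0.051975) = 0.01332 + 0.02098 = 0.0343, so SE = 0.185. Power = Φ(0.530/0.185 − 1.96) = **82%** (unadjusted logistic, Wald test). The uncorrected pooled z-test also gives 82%.

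**Step 3: add a linear trend.** Over 18 monthly points the variance of time is (18² − 1)/12 = 26.92, the variance of the phase indicator is 0.25, and their covariance is 9/4 = 2.25. Hence r² = 2.25²/(26.92·0.25) = 0.752, and the variance of the phase effect is inflated by 1/(1 − 0.752) ≈ 4.0. With the binomial weights the inflation is 3.9 for a common slope and 4.0 for separate slopes. Power = Φ(0.530/SE − 1.96), with the level change taken at the start of the post-intervention phase:

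| Model (binomial logit, 917 per phase) | SE | Power |
|---|---|---|
| Phase only | 0.185 | 82% |
| Level + common slope | 0.365 | 31% |
| Level + slope + slope change | 0.372 | 30% |
| Either trend model, assumed 3-month gap | 0.459 | 21% |
| Either trend model, assumed 9-month gap | 0.66 to 0.68 | 12% |

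**Step 4: checks on the assumptions.**
- Simulation (3,000 runs, no gap) gives 30% and 31% for the binomial models, and 27% to 28% for least squares on monthly proportions.
- Cutting each phase into 18 or 39 points leaves power at 30% to 31%.
- Monthly autocorrelation of 0.2 to 0.4 gives about 26%.
- In the separate-slopes model, testing the effect at the middle of the post-intervention phase gives 17% (risk scale) to 22% (logit scale).
- Using the full 1900 (950 per phase) gives about 31%.
- Reaching 80% with separate slopes and no gap needs about 917·[(1.96 + 0.842)/1.425]² ≈ 3,550 per phase, where 1.425 = 0.530/0.372. The same calculation on the risk scale gives 3,464.

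**The case against.** **The two sentences may describe one analysis.** ITS could be the approach and logistic regression the model for a binary outcome, that is, segmented logistic regression. This is a fair reading, so the text is unclear rather than flatly contradictory. It does not rescue the 0.80: the segmented logistic model is the third row of the table. A univariate logistic comparison of phases also has no trend term, so at least part of the second sentence is a different analysis.

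**A statistical analysis plan may settle the model.** Detail such as the segmented terms and the covariate list can properly be left to it, and its absence here is not the point. Such a plan would not by itself correct section 4.4, where a power is stated that does not apply to the analysis section 10.1 names first.

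**The 30% is conditional.** This stands. The protocol specifies no ITS model. The rates are also uncertain: section 4.4 builds them from yearly rates of major bleeding and thrombosis, while the endpoint in section 8.1.1 adds clinically relevant non-major bleeding and covers the admission plus 3 months. At illustrative rates of 15% against 9%, ITS power would be about 50%; at 20% against 12.2%, about 61%. Lower rates would reduce it.

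**Stronger readings that the document does not support.** A reader might count three rival primary results (ITS, crude, adjusted). Crude followed by adjusted logistic regression is ordinary reporting; the open question is ITS or logistic regression. A reader might also conclude that the logistic model must be primary. The protocol gives no ground for that: without a trend term the model gains power but leaves secular change inside the effect estimate.

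**Conclusion.** The point holds in a conditional form. The 917 per phase is a correct two-proportion calculation, and its power of 0.80 belongs to a before-after comparison without a time trend. Section 10.1 leaves open whether that comparison or ITS decides.

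If a trend-adjusted level change decides, the protocol's own rates give about 30% power, roughly 50 percentage points below the stated figure. Among the trend-adjusted level-change models tried at those rates, this is near the top: the range is about 8% to 31% for gaps of 0 to 12 months. It would be wrong to say that the plan simply has 30% power, since the ITS model, the gap length and the true event rate are all unstated or uncertain. What can be said firmly is that the 0.80 does not carry over to ITS, and that the shortfall at the planning rates is large under every trend-adjusted model examined.

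**What to change.** In section 10.1, state which single analysis decides the primary outcome and label the other supportive. Then make section 4.4 match:

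- **If ITS decides:** replace the 0.80 with the ITS power, shown as a range with its assumptions (model terms, time unit, gap length, autocorrelation, event rates). Restoring 0.80 by recruitment alone would take nearly four times the planned number, so stating the power openly is the realistic course.
- **If adjusted logistic regression decides:** state that the 0.80 applies to that before-after comparison only. Report the ITS level and slope estimates beside it, with confidence intervals, as the check for secular trend. State in advance that a non-significant ITS result is not evidence of no effect.

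The choice is the sponsor's, because it trades power against possible bias from secular change. The cost is wording in two sections and no new data. The first option admits a weakly powered primary test; the second admits a primary estimate that does not itself remove a time trend.

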### **10.2 Secondary study parameter(s)**

For the secondary outcomes linear or logistic regression analysis will be used, depending on the parameter.

To assess differences in patient characteristics for the two periods the appropriate test (t-test, Mann-Whitney U test or Pearson's chi-square test) will be used.

### **10.3 Other study parameters**

N.a.

### **10.4 Interim analysis (if applicable)**

N.a.

## 11. ETHICAL CONSIDERATIONS

### 11.1 Regulation statement

This study will be conducted according to the principles of the Declaration of Helsinki (version October, 2013) and in accordance with the Medical Research Involving Human Subjects Act (WMO).

### 11.2 Recruitment and consent

#### Pre-intervention phase:

At discharge the patient (or the parents/guardian of the patient) will be asked to fill out a consent form. By signing the consent form, the patient (or the parents/guardian of the patient) gives permission to retrieve patient data from the community pharmacist and the general practitioner.

After the patient (or the parents/guardian of the patient) has signed the consent form, he or she receives four small questionnaires 3 months after hospitalization. The questionnaires concern the quality of life, the quality of care (patient satisfaction with antithrombotic therapy), the adherence to drug treatment and the use of healthcare. It will take about 15-20 minutes to fill out the questionnaires.

If the four questionnaires are not returned within two weeks, we will contact the patient by telephone. The questionnaires will then be conducted by telephone.

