### 4.2 Inclusion criteria

In order to be eligible to participate in this study, a subject must meet all of the following criteria:

- Patients that are or will be treated with antithrombotics in the Erasmus MC or in the Reinier de Graaf hospital.
- Informed consent (we will ask permission from the patients to collect community pharmacy and to fill out four questionnaires).
- Only the first hospital admission of a patient within the study period will be included (readmission is an endpoint).

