### 4.3 Exclusion criteria

A potential subject who meets any of the following criteria will be excluded from participation in this study:

- No informed consent
- Patients admitted for one day
- Patients admitted to the Intensive Care Unit
- Patients treated with low molecular weight heparins monotherapy for thrombosis prophylaxis
- Patients enrolled in a clinical trial of antithrombotic therapy
- Patients treated with phytomenadione used for the prevention and treatment of vitamin K deficiency
- Patients treated during hospitalization with a single dose of the antithrombotic agents

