|                 | Overview of medication use three months after hospitalization (coded with ATC-code  )+                                                                                                                                                                                                                                                                                                                                                                                                                                                                                                                                        |

\*Obtained from medical record of the hospital information system

+Obtained from the community pharmacist and the Thrombosis Service

\$Obtained from the patient using questionnaire

^Obtained by sending a small questionnaire asking for visits to the general practitioner or hospital because of a bleeding or thrombotic event within 3 months after hospitalization.

***The primary outcome of the study is the proportion of patients with a composite endpoint consisting of  $\geq 1$  bleeding (major bleeding and mild to moderate clinical relevant non-major bleeding) or  $\geq 1$  thrombotic events during and 3 months after hospitalization.***

Patients treated with antithrombotics and/or antidotes in the Erasmus MC and in the Reinier de Graaf hospital will be included with the help of a clinical rule (table 1 and 2). The data from the medical record of the hospital information system is used to determine whether there is a bleeding (major bleeding and mild to moderate clinical relevant non-major bleeding) or thrombotic event in patients who are enrolled in the study.

After hospitalization data from community pharmacist, general practitioner and the Thrombosis Services are used. At discharge the patient will be asked to fill in a consent form. By signing the consent form, the patient gives permission to retrieve patient data from the community pharmacist, general practitioner and the Thrombosis Services.

Definition of terms:

The ISTH definitions of bleeding in patients are as follows:

- Major Bleeding in non-Surgical Patients
  - 1. Fatal bleeding, and/or
  - 2. Symptomatic bleeding in a critical area or organ, such as intracranial, intraspinal, intraocular, retroperitoneal, intra-articular or pericardial, or intramuscular with compartment syndrome, and/or

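### Consent is a condition of inclusion but is asked only at discharge, so deaths and fatal bleeds during the index stay cannot enter endpoints that are defined to count them

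*Protocol*

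**What the plan says.** **Eligibility.** Section 4.2 requires that "a subject must meet all of the following criteria", and one of these is "Informed consent (we will ask permission from the patients to collect community pharmacy and to fill out four questionnaires"). Section 4.3 repeats the condition as an exclusion: "No informed consent".

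**Time of consent.** Section 11.2 gives one moment, in identical words for both phases: "At discharge the patient (or the parents/guardian of the patient) will be asked to fill out a consent form". Section 8.3.1 says the same. The only proxy named is a parent or guardian. No waiver, deferred consent or next-of-kin route is described for a patient who dies in hospital.

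**Other exclusions in 4.3.** These include "Patients admitted to the Intensive Care Unit", "Patients treated during hospitalization with a single dose of the antithrombotic agents", and admissions of one day.

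**Endpoints.** The primary endpoint (8.1.1) runs from the start of antithrombotic medication, or from hospitalization, to three months after hospitalization. The first criterion for major bleeding, in non-surgical and in surgical patients, is "Fatal bleeding, and/or". On mortality, 8.3.1 states: "We define all-cause mortality as death from any cause during and 3 months after hospitalization".

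**Data sources.** Section 8.3.1 identifies patients with a clinical rule and collects case report data during the stay for each included patient. Section 11.4 describes everything except the questionnaires as retrospective screening of medical records.

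**The concern.** Membership of the cohort is settled at the end of the index stay, while the outcome window opens at or near its start. A patient who dies in between meets an exclusion and is lost with whatever event caused the death. The protocol thus defines outcomes that its own eligibility rules prevent from being observed.

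Two consequences follow. First, the endpoints are truncated: in-hospital mortality cannot be estimated, and a reduction in fatal in-hospital bleeding or thrombosis could not be seen. Second, the comparison has no randomization to protect it. In the post-intervention phase the S-team acts before the point at which eligibility is settled. If it changes who dies, who is transferred, who stops after one dose or who agrees to take part, the two cohorts are selected differently. Covariate adjustment cannot restore patients who were never enrolled.

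**Working it through.** **Step 1. Eligibility rules against outcome windows.**

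| Event | Does it count as written? | Reason |
|---|---|---|
| Death or fatal bleed in the index stay | No | No discharge, so no consent (4.2, 4.3, 11.2) |
| Death or fatal bleed after discharge, within 3 months | Yes, if the patient consented | Inside both windows (8.1.1, 8.3.1) |
| Severe non-fatal event in hospital | Yes, if discharged, consented and no exclusion applies | Inside the primary window |
| Event after one dose, drug then stopped | No | Single-dose exclusion, known only later |
| Event ending a one-day stay | No | One-day exclusion, known only later |
| Event leading to ICU transfer | Unclear | 4.3 does not say whether direct admission or any later transfer is meant |

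The first row contradicts 8.1.1, the bleeding definition and the mortality definition. It needs no numerical assumption.

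**Step 2. The plan's own sample size (4.4).** Inputs: 9% against 5.5%, alpha 0.05, power 0.80. Sidedness is not stated; two-sided is used here. With mean rate 0.0725 and difference 0.035:

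n = [1.960·√(2·0.0725·0.9275) + 0.8416·√(0.09·0.91 + 0.055·0.945)]² / 0.035² = 860.5, that is 861.

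With the continuity correction, n/4·[1 + √(1 + 4/(n·0.035))]² = 916.8, that is 917. The stated figure is reproduced. Power at 917 per phase without the correction is 82.4%.

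**Step 3. Illustration of truncation.** The protocol gives no in-hospital death rate and no share of events lost. Assume that a share f of patients with a composite event is lost, equally in both phases, and that they are replaced by further recruitment. Each rate p then becomes p(1−f)/(1−pf). For f = 30%: 0.063/0.973 = 6.5% and 0.0385/0.9835 = 3.9%.

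| f (assumed) | Pre | Post | n per phase, with correction | Power at 917, without correction |
|---|---|---|---|---|
| 0 | 9.0% | 5.5% | 917 | 82.4% |
| 5% | 8.6% | 5.2% | 959 | 80.8% |
| 10% | 8.2% | 5.0% | 1005 | 78.9% |
| 20% | 7.3% | 4.5% | 1115 | 74.6% |
| 30% | 6.5% | 3.9% | 1256 | 69.5% |

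**Step 4. Illustration of unequal loss.** Assume no true effect, with 9% in both phases. Losing 10% of events before and 20% after gives 8.17% − 7.33% = 0.84 points of spurious reduction. Losing 10% before and 30% after gives 8.17% − 6.47% = 1.70 points, about half of the planned 3.5. With 20% lost before and 10% after, the sign reverses (−0.84). The protocol does not say whether the losses would differ, or in which direction.

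**The case against.** The best reply is that consent was never meant to govern in-hospital data. Its stated scope is outside records and questionnaires, the clinical rule finds patients during the stay, case report data are collected before consent is asked, and 11.4 calls the rest record screening. That may well be the intent, and it makes the repair easy. It does not settle the matter, because 4.2 and 4.3 make consent a condition of inclusion without limiting it to outside data, and the case report form is for included patients.

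A second reply is that the same rules apply in both phases. That stands in part: they mainly truncate the endpoints. They bias the contrast only if the S-team changes who is lost. An effect on willingness to consent is plausible but unproven.

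A reader might infer more than the text supports:

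- **That no fatal bleed, and none of the severest events, can count.** Post-discharge deaths and fatal bleeds do count, and so do severe non-fatal in-hospital events under the conditions in Step 1.
- **That every patient transferred to the ICU because of an event is excluded.** That is one reading of a criterion without timing.
- **That lost events can be counted within the planned 917.** Assuming 2% to 5% in-hospital deaths, 20% to 50% of them with an event, gives 917 × 0.02 × 0.20 = 3.7 to 917 × 0.05 × 0.50 = 22.9, against 917 × 0.09 = 82.5 expected. But the 917 are consenting patients, of whom those who died in hospital were never part. Nor should a loss in one phase be set beside the planned between-phase difference of 917 × 0.035 = 32: an equal loss of 28% would shrink that difference by about 9, to 23.

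**Conclusion.** The contradiction is in the protocol's text and does not depend on any assumed rate. Followed literally, the plan returns zero in-hospital deaths in both phases and a composite without in-hospital fatal bleeds, while describing both endpoints as covering the stay. The single-dose and one-day exclusions add selection on later events. The ICU exclusion may do so, depending on what was meant.

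The size of the loss in the composite cannot be derived from the document. Under the assumed equal loss of 5% to 30% of events, uncorrected power at 917 per phase falls from 82.4% to between 80.8% and 69.5%. Bias in the before/after contrast is possible in either direction, but it requires the intervention to change who is lost. This is more than missing detail, because patients lost in this way cannot be recovered at analysis.

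**What to change.** 1. In 4.2 and 4.3, limit the consent condition to data from the community pharmacy, the general practitioner and the Thrombosis Service, and to the questionnaires.
2. With the agreement of the ethics committee (METC), count in-hospital bleeding, thrombosis and death from the hospital record for all patients identified by the clinical rule and otherwise eligible. This is the record screening that 11.4 already describes.
3. Define the ICU, single-dose and one-day exclusions by status or intention at first identification, in the same words for both phases, so that later transfers, stops and deaths stay in.

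The cost is an ethics amendment and reworded criteria. Moving all consent to the time of identification is not needed. It would add work, since patients later excluded would also be approached, and in the post-intervention phase consent could still follow contact with the S-team.

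If the committee does not agree to step 2, restate the primary and mortality endpoints as applying to patients who were discharged alive and consented, and drop the claim to cover death in hospital.
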